**AIM 2: Evaluate the impact of Resilience Project blight remediation activities on fatal and non-fatal opioid overdose.**

- a. **Rationale:** The blight remediation efforts taking place in Kensington as part of the Resilience Project may have an immediate impact on drug use behavior, which could result in fewer overdoses. For example, remediating abandoned buildings reduces the number of semi-private but easily accessible physical spaces in which drugs could being used. Abating vacant lots could affect the experience of stress in the neighborhood, which could result is less drug use.
- b. **Study site and design:** This is a community level difference-in-differences study of the impact of blight remediation on opioid overdose outcomes taking place in the Kensington neighborhood (same location as Aim 1).
- c. **Intervention:** The blight remediation activities included in this proposal are abandoned house remediation and vacant lot abatement. We will obtain the date, time, and exact geographic location of all blight remediation activities from the City of Philadelphia. At the start of the study, we will receive a list of activities to date, followed by a monthly report of all activities in the previous 30 days. Abandoned house remediation involves cleaning and properly sealing abandoned houses with secure plywood (clean and seal). This intervention is performed by the Department of License and Inspection. To date, 95 houses have received this intervention. In addition, these houses are also eligible to get a “doors and windows” intervention, which in involves painting doors and windows on the plywood, which gives the appearance that the house in lived in. This intervention is performed by the Community Life Improvement Program (CLIP). To date, 64 houses have received this intervention. See Figure 8 (previous page) for two before/after examples. Finally,

vacant lot abatement involves clearing trash from the lot. A select number of lots will also receive a clean and green intervention, similar to the intervention studied by our team, which involves grass seeding, erecting a low wooden post-and-rail fence, and monthly maintenance.

- d. **Comparator Group:** For each blight remediation activity, we will randomly select two comparator locations that are at least 0.25 miles away that were eligible for but did not receive blight remediation in the 30 days prior to the intervention activity. The first comparator location will be in the Kensington zip code (comparator 1), allowing for a comparison in the neighborhood in which all Resilience Project activities are taking place. This will also allow us to evaluate if blight remediation can be linked to an absolute decrease in overdose without simply pushing drug use and overdose to a different location. The second comparator location will be outside the Kensington neighborhood in one of the immediately adjacent zip codes (comparator 2). This comparator allows us to evaluate the impact of blight remediation activities in a location where no Resilience Project efforts are taking place in order to account for any co-linear associations that may be due to other resilience project interventions but are independent of blight remediation.

We will use the ArcGIS tool Similarity Search to randomly pick the two comparator locations with unremediated abandoned houses or vacant lots for each blight remediation intervention location. Using the tool, we will first find a block group either within Kensington (comparator 1) or immediately outside of Kensington (comparator 2) that has the same sociodemographic profile of the matched blight remediation area, but did not receive remediation. We will then determine the geographic center of each selected block group, which will serve as the point locations around which outcomes are measured.

**AIM 3: Evaluate implementation of the Resilience Project by a) characterizing the fidelity of the AR2 intervention in Kensington, b) measuring factors that moderate AR2 fidelity, including blight, c) assessing barriers and facilitators to AR2 implementation, and d) determining the costs for AR2 and blight remediation interventions.**

- a. **Rationale and theoretical framework:** As with many interventions, the AR2 comprises a complex repertoire of behaviors in which staff must engage. The AR2 will deploy with different staff compositions and deliver different combinations of core components in each encounter. In order for the AR2 to be implemented as designed (fidelity), it is essential to understand which malleable factors – including neighborhood blight – modify its implementation. Assessing costs and resource use of both the AR2 and blight remediation is also critical to inform future efforts to implement, disseminate, and spread these interventions.

The measurement and analyses for Aim 3 are guided by the Consolidated Framework for Implementation Research (CFIR). CFIR identifies intervention characteristics, factors outside the organization (outer setting), factors inside the organization (inner setting), provider characteristics, and processes that may affect implementation. Figure 9 shows the CFIR framework adapted for the proposed study. We will

measure use of six aspects of the AR2 for which it was designed to perform (fidelity). We will also characterize inner and out setting factors, individual provider characteristics and aspects of the AR2-patient engagement that may affect this implementation outcome. For example, the presence of a social worker (inner setting) at the time of engagement may increase the probability of treatment referral. Knowledge, self-efficacy and beliefs about the AR2 by its providers (individual) could impact how they engage with people who overdose. The presence of street blight (outer setting) could add stress, fear, and a sense of chaos to the AR2 encounter, affecting both the AR2 team and the overdose victim, limiting engagement.

- b. **Characterize which AR2 components are completed (fidelity).** First, we will use the established AR2 database to characterize which AR2 dispatches result in: 1) dispensation of take-home naloxone, 2) referral to a treatment facility that has immediate availability and can provide MAT, 3) transportation to a treatment facility, 4) family engagement, 5) collection of patient telephone information, and 6) telephone follow up within 7 days of encounter. Last, we will characterize which AR2 dispatches lead to any interaction with the individual who experienced the overdose (as some persons leave the scene after being administered naloxone by police, EMS, or a bystander). AR2 staff record each of these variables in real-time for each AR2 dispatch. Data are imported into a secure database and stored at Philadelphia Fire Department headquarters.
- c. **Measure factors that moderate AR2 fidelity, including blight.** We will characterize the extent to which select inner and outer setting factors as well as individual and process characteristics are associated with 1) any AR2 patient engagement, 2) overall fidelity, and 3) individual fidelity components. The outer setting characteristics we will explore are neighborhood environmental characteristics measured through direct observation within 72 hours of each AR2 engagement for engagements that occur after IRB approval of the study. The most relevant and malleable inner setting factor is staffing combination (e.g. presence or absence of social worker, CRS, and/or caseworker for each AR2 encounter). Neighborhood environmental characteristics (outer setting) will be measured as follows. Each morning, we will obtain a list of the exact geographic location of all prior day's AR2 engagements from the AR2 team; similar to past work from our team, a trained study field team will then visit those locations that afternoon to take a full set of photographs, which will be uploaded and stitched into 360° high-resolution panoramas using Microsoft Photosynth software. (Figure 10, previous page). Photographs will be taken within 72 hours of the AR2 engagement and we anticipate minimal change in environment during that period. Trained coders will code all photographs for level of blight using a code book developed by our team for prior work. We will focus on visible elements of the neighborhood environment that we expect to be modifiable based on the Resilience Project blight remediation activities including trash, building conditions, vacant lots, and graffiti. Each photograph will be coded by two coders and discrepancies resolved by consensus.

Our primary interest is in studying the correlation between our blight measure and AR2 fidelity. We will regress fidelity on our measure of blight, testing whether high levels of blight are associated with lower program fidelity. We expect the AR2 to have 300-500 engagements per year. The Kensington zip code has 2,160 intersections, approximately the total number of unique outdoor locations. However, we do not expect that these intersections are equally likely to have overdoses. We simulated 366 overdoses occurring at these intersections, such that some intersections could have 10 overdoses, while most intersections have 0. This unequal chance of an overdose at each intersection does not induce clustering, but it does limit the observed variation in blight measures. We simulated in such a way that the most blighted intersections are the ones to have the most overdoses. Then we considered a test of correlation (or equivalently, a linear regression) between our blight measure and our fidelity measures. We have sufficient power to detect correlations more negative than -0.10.

Staffing combination (inner setting) is self-recorded by the AR2 providers. Due to varying AR2 staffing from shift to shift, we anticipate variability in dosage and fidelity by different crews, which will be unconfounded with encounter features, conditional on time and place. Our primary approach will be regression models, logistic regression for 0/1 outcomes and a proportional hazards model for time-to-event outcomes, in which our measures of dosage and fidelity are covariates. The power calculations for these analyses are identical to the Aim 1 power analysis for comparisons across time discontinuities. Rather than comparing across time periods, we will be comparing across high/low dose and high/low fidelity. Certain patients may be more receptive to AR2 services causing the AR2 to provide a greater dosage and maintain higher fidelity to the AR2 model. While we have no direct measure of “receptivity,” we will use a collection of patient features potentially correlated with receptivity including patient substance abuse profile, number of prior overdoses, age, race, and sex. We will use propensity score weighting to reweight high dosage patients so their features collectively resemble the features of low dose patients. Outcome models using these weights will estimate the treatment effect of receiving a low dose, answering what would happen to low dose patients if instead they were give a high dose of AR2 services. Similarly, we can reweight patients receiving high fidelity AR2 response to resemble low fidelity AR2 response, so that the outcome model estimates the effect of receiving low fidelity for those patients who actually received low fidelity AR2. Although dosage and fidelity are not 0/1 measures, we will consider dichotomizing them if high/low dosage and high/low fidelity have clear boundaries in practice.

- d. **Evaluating barriers and facilitators to AR2 implementation:** In order to supplement the approach to implementation analysis described above, we aim to add a qualitative approach to understanding and describing provider and process level individual perspectives that may influence implementation. This additional approach acknowledges that, while guided by theoretical implementation frameworks, a purely quantitative approach could miss important contextual aspects of implementation that

were not captured in the quantitative measures. We will conduct individual semi-structured interviews with the AR2 team (n=40). Informed by the Theory of Planned Behavior, we will assess the range of perceptions related to norms, attitudes, beliefs, knowledge, and perceived behavioral control focused on patient engagement and delivery of AR2 services. The interview guide will be framed around assessing “which parts of the AR2 seem to work and which do not” and how the team plans and reflects on processes for improving implementation. Interviews will be conducted and audio-recorded via Zoom by staff trained in qualitative interviewing. Transcripts will be entered into NVivo 12.0 (QSR, Doncaster, Australia) for analysis. Analysis will be overseen by [name] who has extensive experience in conducting and analyzing qualitative interviews. Using modified grounded theory, members of the team will discuss the transcripts and create a codebook. Two study staff will pilot and then fully and separately code the transcripts. Analytic memos will be created for all nodes, describing key themes and a comprehensive list of relevant quotations from interviewees. Using the constant comparison methods, in which newly collected data will be compared with categories that emerge from previously collected data, all memos will be analyzed for consistency and disagreement. We will also examine differences in concepts for interviewees by their profession (e.g., social worker or paramedic).

- e. **Measure program costs:** We will determine the cost of the AR2 and the blight remediation interventions from the perspective of the City of Philadelphia, including its Department of Public Health and Fire Department. This portion of the project will be conducted with guidance from colleagues at CHERISH, the NIDA-funded multi-institutional substance use treatment health economics center, for which [name] (mPI) leads the Policy and Dissemination Core. Our approach will follow standard micro-costing methods. Micro-costing is a technique in which all inputs consumed in an intervention are identified and quantified in detail; then these resources are converted into pecuniary terms to produce a cost estimate. It is most appropriate when there are no alternative data sources because an intervention is novel and services are not always reimbursed. Resources will include personnel time, travel costs, and materials directly used by the AR2 and blight remediation programs, and these resources will be valued based on salaries, benefits, and other unit costs provided by the relevant City of Philadelphia departments. To facilitate national comparisons, we will also value personnel costs at standard wage and fringe benefit rates for relevant personnel categories published by the U.S. Bureau of Labor Statistics. Supervision and other overhead costs will be estimated based on interviews with City of Philadelphia staff members. The results of this analysis will inform future decisions regarding sustaining implementation and expansion of these novel place-based interventions for delivering harm reduction and care linkage services for a uniquely vulnerable population of patients who overdose.

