2  
3 **PRINCIPAL INVESTIGATORS:** [name] MS, [name] MS

4 **PROTOCOL TITLE:** Studying the PhilAdelphia Resilience Project as a Response to Overdose  
5 (SPARROw)

6  
7 **1. INTRODUCTION AND PURPOSE:**

8  
9 **1.1. Objectives:** The objective of this proposal is to evaluate the effectiveness and  
10 implementation of two City of Philadelphia Resilience Project programs to reduce  
11 opioid overdose: (1) the Alternative Response 2 (AR2) that accompanies ambulances  
12 responding to overdoses and aims to deliver harm reduction and care linkage to people  
13 who refuse hospital transport, and (2) blight remediation of abandoned buildings and  
14 land. This application leverages a natural experiment within the Resilience Project  
15 implementation to evaluate its impact on overdose outcomes.

16  
17 We propose to address the following Specific Aims:

18  
19 **SA1: Determine the effectiveness of the Resilience Project AR2 on opioid overdose**  
20 **outcomes for EMS patients who refuse hospital transport after overdose.** Using a  
21 quasi-experimental design, we will compare the proximal overdose outcomes (rates and  
22 timing of treatment linkage) and distal overdose outcomes (non-fatal overdoses within  
23 60 days and overdose deaths within 24 months) for patients who receive AR2  
24 engagement compared to those who, due to timing or location restrictions, receive  
25 traditional EMS care alone.

26  
27 **SA2: Evaluate the impact of Resilience Project blight remediation activities on**  
28 **fatal and non-fatal opioid overdose.** Blight remediation activities vary across time and  
29 space in Kensington. We will use a difference-in-difference design to compare fatal and  
30 non-fatal overdoses in the 60 days before and after any given remediation effort  
31 compared to the same time period in two nearby locations that did not get remediated  
32 but had comparable pre-blight remediation overdose rates. We will select one control  
33 location from within Kensington and one just outside the Resilience Project geographic  
34 boundary.

35  
36 **SA3: Evaluate implementation of the Resilience Project by a) characterizing the**  
37 **fidelity of the AR2 intervention in Kensington, b) measuring factors that moderate**  
38 **AR2 fidelity, including blight, c) assessing barriers and facilitators to AR2**  
39 **implementation, and d) determining the costs for AR2 and blight remediation**  

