## **AIM 2 Analysis:**

- a. **Analysis plan and power calculation.** We will analyze separately abandoned home remediation and vacant lot abatement, but both will have a similar analysis structure. We will use a conditional Poisson regression model of the form  $\log(E(\text{count})) = \beta_0 + \beta_1 \text{clean} + \beta_2 \text{post} + \beta_3 \text{clean} \times \text{post}$ , where clean is a 0/1 indicator of whether the location went through blight remediation and post is a 0/1 indicator of whether the time period measured is post-blight remediation in the treated location. The conditional Poisson model accounts for the matched pairs of location.  $\exp(\beta_3)$  is of

primary interest, a ratio of rate-ratios, contrasting the relative change in overdose rates in the treated area pre- versus post-remediation with the relative change in overdose rates in the comparison locations.

We anticipate at least 55 blight remediated locations with which we can pair with 55 un-remediated locations. The average buffer area will have 1.2 overdoses per month. Under such circumstances we will be able to detect reductions of 50% or more in overdose rates with power 0.80.

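### The Aim 2 comparator rules conflict on remediation-free period, matching variable and measurement point, so the control can be contaminated and unlike the remediated sites

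*Protocol*

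**What the plan says.** Protocol section 1.1 (SA2) counts fatal and "non-fatal overdoses in the 60 days before and after any given remediation effort", "compared to the same time period in two nearby locations that did not get remediated" "but had comparable pre-blight remediation overdose rates".

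Section 3.1, AIM 2, d (Comparator Group) gives the working rules. A comparator must lie at least 0.25 miles away, be eligible for remediation, and be one that "did not receive blight remediation in the 30 days prior to the intervention activity". Comparator 1 lies inside the Kensington zip code. Comparator 2 lies in an adjacent zip code, described as having no Resilience Project activity. The search then looks for unremediated houses or lots, and the block group chosen is one that "has the same sociodemographic profile of the matched blight remediation area, but did not receive remediation". Finally: "We will then determine the geographic center of each selected block group, which will serve as the point locations around which outcomes are measured".

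Section 3.1, AIM 2, c says the City will supply the date, time and exact location of every remediation activity.

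Section 5.5, AIM 2 Analysis takes exp(β3), a ratio of rate ratios from a conditional Poisson model, as the quantity of primary interest. It assumes 55 remediated locations paired with 55 others at 1.2 overdoses per buffer per month and states that "we will be able to detect reductions of 50% or more in overdose rates with power 0.80".

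**The concern.** These rules define the control group, and so they define exp(β3). They do not agree on three matters: how long a comparator must be free of remediation, what it is matched on, and where its outcomes are counted. Two teams, one following section 1.1 and the other section 3.1, would build different control sets.

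A comparator that is itself remediated inside the outcome window shares part of the treatment, which pulls the estimate toward no effect. A comparator chosen without regard to overdose history lacks the safeguard that the aims promise. A comparator buffer centred on a block-group centroid need not be near any eligible house or lot, so it may not describe the kind of place that was remediated.

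**Working it through.** **Inputs.** 60-day windows on each side (section 1.1). A 30-day eligibility look-back (section 3.1). 55 pairs, 1.2 overdoses per buffer per month, a 50% reduction and power 0.80 (section 5.5). Alpha and sidedness are not stated for Aim 2; Aim 1 uses one-sided 0.05, so I tried one- and two-sided 0.05. The share of comparators remediated within the window is not given; I assume 10-40%.

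**1. The plan's power figure.** With four Poisson cells and μ expected events per untreated cell, SE of the log ratio = √(3/μ + 1/(0.5μ)), and power = Φ(0.693/SE − z).
- One-month windows: μ = 55 × 1.2 = 66, SE = 0.275. Power is 0.809 one-sided and 0.712 two-sided. The one-sided value reproduces 0.80.
- 60-day windows: μ = 132, SE = 0.195. Power is 0.972 one-sided and 0.945 two-sided.
- One-month windows with two comparators per site: SE = √(1/66 + 1/33 + 2/132) = 0.246. Two-sided power is 0.804.
- 60-day windows with variance inflated 1.6-fold: SE = 0.195 × √1.6 = 0.246, two-sided 0.804. Inflated 2-fold: SE = 0.275, one-sided 0.809.

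Several sets of inputs therefore give 0.80, and the text does not say which was used.

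**2. Days covered by the dated rule.** It covers days -30 to -1, which is 30 of 120. Days -60 to -31 (30 days) and the whole post period (60 days) have no dated condition.

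**3. Effect of contamination.** Let f_pre and f_post be the shares of comparator exposure that fall after the comparator's own remediation, with the same true effect RR = 0.50. Then

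observed ratio = RR × [1 − f_pre(1 − RR)] / [1 − f_post(1 − RR)].

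For a share s of comparators remediated:
- Spread evenly over the 60 days after (f_post = s/2, f_pre = 0): s = 0.1 gives 0.5/0.975 = 0.513; s = 0.4 gives 0.5/0.90 = 0.556.
- All at the start of the post window (f_post = s): 0.5/0.95 = 0.526; 0.5/0.80 = 0.625.
- Spread evenly over days -60 to -31 (f_post = s, f_pre = 0.75s): 0.5 × 0.9625/0.95 = 0.507; 0.5 × 0.85/0.80 = 0.531.

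At s = 0.4, the 60-day one-sided power of 0.972 falls to 0.91 with even spread (SE = 0.197, Φ(0.588/0.197 − 1.645)) or 0.76 at the start (SE = 0.199, Φ(0.470/0.199 − 1.645)).

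These figures are for a contrast with comparator 1. If an uncontaminated comparator 2 is pooled with equal weight, f_post halves: 0.506-0.526 with even spread, 0.513-0.556 at the start.

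**4. Unequal overdose levels.** If comparators have half the overdose level but the same trend, the ratio of rate ratios is unchanged. Only precision suffers: SE = √(1/132 + 1/66 + 2/66) = 0.230, and one-sided 60-day power is 0.914.

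**5. Matching and measurement point.** Section 1.1 requires similar prior overdose rates; section 3.1 names sociodemographic profile and does not mention overdose. Section 4 gives a third description, with randomly selected control lots matched to treated lots. Section 3.1 first looks for places with an unremediated house or lot, then counts around the block-group centre. The centre of the remediated sites' buffers is not spelled out, but their exact coordinates are obtained, so counting around the property is the natural reading.

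**The case against.** The strongest reply is that the plan does not settle on a 30-day rule. Section 1.1 says comparators were not remediated, and section 3.1 adds that the block group "but did not receive remediation". Read over the full window, that wording excludes a site remediated on day +10. This stands: a reader might infer that the design knowingly admits remediated comparators, and the documents do not show that. But the excluding phrases in section 3.1 carry no dates, and an analyst applying the one dated rule could admit such a site.

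Two further replies also stand. Comparator 2 lies where the programme is not active, so contamination concerns mainly comparator 1. And because all activity dates and locations are obtained, contaminated comparators can be found and dropped or censored; the bias is not beyond repair afterwards.

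A reader might also infer that failing to match on overdose rate must produce a spurious benefit through regression to the mean. The documents do not support this. They do not say that sites are chosen on recent overdose counts, and difference-in-differences needs parallel trends rather than equal levels. Nor would matching on an earlier period cure such selection: the remediated sites' pre-period count would still be selected high and the comparators' would not.

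Finally, the stated power might be taken as wrong for 60-day windows. It cannot be called wrong, since a 60-day calculation with modest overdispersion also gives 0.80. If one month was used without overdispersion, the claim is conservative.

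**Conclusion.** The three conflicts are confirmed from the text and should be reconciled. Followed as section 3.1 reads, the rules can give a control that is partly remediated and is not measured like the remediated sites; they do not establish that it will be.

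Contamination would bias exp(β3) toward 1. The 0.51-0.56 and 0.53-0.63 ranges rest on an assumed 10-40% of comparators remediated, a true ratio of 0.50, an equal effect at comparators and a contrast with comparator 1; pooling with comparator 2 makes them smaller. The matching conflict removes a stated safeguard on comparability but is not itself a demonstrated bias. The centroid rule is a difference in how the areas are built, whose effect the documents do not allow one to size. The power figure is under-specified rather than wrong.

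**What to change.** - State one dated rule: no remediation within the comparator's buffer from day -60 to day +60 of the index activity, or censor the comparator at its own remediation. The activity dates already obtained are enough to apply it.
- State one selection rule, the same in sections 1.1, 3.1 and 4, that includes prior overdose rate or trend as section 1.1 promises, and check pre-period trends.
- Centre each comparator buffer on an eligible unremediated house or lot, and say that remediated sites' buffers are centred in the same way.
- State the window length, alpha, sidedness, dispersion and number of comparators behind the Aim 2 power figure.

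The cost is protocol wording and a run of the location search under the new rule, on data the study already plans to hold. The downside is that fewer comparators will be eligible, mainly inside Kensington.

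### Aim 2 draws from each comparator a conclusion that its contrast cannot support: comparator 1 cannot rule out displacement, and comparator 2 does not net out other Resilience Project programs

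*Protocol*

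**What the plan says.** Section 3.1, Aim 2, d. Comparator Group, describes two comparators for each remediation. The plan will "randomly select two comparator locations that are at least 0.25 miles away".

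- **Comparator 1.** "The first comparator location will be in the Kensington zip code (comparator 1"). Its first stated use is a comparison within the neighborhood where all the programs run. The section then adds that it will show whether remediation gives an "absolute decrease in overdose without simply pushing drug use and overdose to a different location".
- **Comparator 2.** "The second comparator location will be outside the Kensington neighborhood in one of the immediately adjacent zip codes (comparator 2"). The section describes it as free of Resilience Project activity and gives its purpose as "in order to account for any co-linear associations that may be due to other resilience project interventions but are independent of blight remediation".

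Section 5.5, Aim 2 Analysis, fits a conditional Poisson model with a treated indicator (clean), a period indicator (post) and their product. It makes exp(β3) primary: "a ratio of rate-ratios, contrasting the relative change in overdose rates in the treated area" with the relative change in the comparison locations. Section 1.1 (SA2) sets the windows at 60 days before and 60 days after. The difference-in-difference part of the Aim 1 analysis in section 5.5 states that the AR2 does not operate outside zip code 19134.

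**The concern.** Each rationale sentence says what a contrast will establish, and the model can be checked against it.

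The displacement sentence relies on a location whose count is the denominator of the estimate. If drug use moves there, the estimate shows more benefit. If drug use moves anywhere else, the estimate does not register it.

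The sentence on other programs relies on a location that those programs do not reach. A control removes the effect of a concurrent influence only if it shares that influence.

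Displacement is a realistic possibility here. The Aim 2 rationale is partly that remediation removes accessible places in which drugs are used. Section 6.8 plans to share interim results on blight remediation with the City to inform prevention. Relocated overdoses could then be reported as prevented, or the effect of another Kensington program credited to remediation.

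**Working it through.** **Inputs from the protocol.** 55 treated and 55 comparison locations and 1.2 overdoses per buffer per month (section 5.5, Aim 2); 60-day windows (section 1.1). Expected count per pre-period cell: 55 × 1.2 × 2 = 132. The Aim 2 text gives no alpha or sidedness, so one-sided 0.05 (as in Aim 1) and two-sided 0.05 are both shown. Displacement shares and program effects are assumptions.

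**The plan's own figure.** It states power 0.80 for a 50% reduction. Using SE(β3) = √(sum of 1/expected count over the four cells) and power = Φ(|ln 0.5|/SE − z):

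- 60-day windows, cells 132, 132, 132, 66: SE 0.195, power 0.972 (one-sided) or 0.945 (two-sided).
- One-month windows, cells 66, 66, 66, 33: SE 0.275, power 0.809 (one-sided) or 0.712 (two-sided).

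So 0.80 is matched with one-month windows and a one-sided test, and is conservative for 60 days. The point does not depend on this figure.

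**Estimand.** exp(β3) = (treated post/pre) ÷ (comparator post/pre).

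**(1) Displacement.** Suppose remediation moves 25% of treated-site overdoses (33 of 132) and prevents none. A share s lands in the comparator 1 buffer and the rest elsewhere. Then exp(β3) against comparator 1 = 0.75/(1 + 0.25s). The last column is the combined change, treated plus comparator 1 against an unaffected comparator 2: (0.75 + 1 + 0.25s)/2.

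| s | versus comparator 1 | treated + comparator 1, versus comparator 2 |
|---|---|---|
| 0 | 0.75 | 0.875 |
| 0.25 | 0.71 | 0.906 |
| 0.50 | 0.67 | 0.938 |
| 1 | 0.60 | 1.00 |

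The true net change is zero in every row. Of the 25% to 40% apparent reduction, 25 points are the local fall itself; the inflation specific to comparator 1 is 4, 8 or 15 points for s = 0.25, 0.50 or 1. The combined contrast moves toward 1 as more displaced overdoses are captured, but reaches 1 only if all of them are.

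**(2) Other programs.** Suppose remediation does nothing, and other programs multiply the Kensington rate by g between the pre and post windows.

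- Versus comparator 1: g/g = 1.00 for every g.
- Versus comparator 2: g/1 = g.

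For comparator 2, SE = √(3/132 + 1/(132g)):

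| g | ratio versus comparator 2 | chance of a false benefit, one-sided 0.05 | two-sided 0.05 |
|---|---|---|---|
| 0.9 | 0.90 | 0.15 | 0.09 |
| 0.8 | 0.80 | 0.34 | 0.24 |
| 0.7 | 0.70 | 0.62 | 0.50 |

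A program effect present equally in both windows gives g = 1 and no bias.

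**The case against.** The strongest case on the other side has five parts.

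- **The roles are not simply reversed.** A reader might infer that the plan has swapped its two comparators. The text does not support this. Comparator 1's first stated use is the within-neighborhood comparison, which is the role that nets out other programs. Only the added displacement claim and the comparator 2 rationale fail.
- **Constant program effects cancel.** This stands. Bias against comparator 2 needs an effect that changes within the windows, for Kensington relative to the adjacent zip codes and often enough across staggered remediation dates to matter. The protocol does not show that this happens, and the values of g are illustrative.
- **The inflation may be small.** A reader might take the whole 29% to 40% reduction at s = 0.25 to 1 as bias from comparator 1. Most of it is the local fall. Comparator 1 is one location at least 0.25 miles away, in a zip code with 2,160 intersections (section 3.1, Aim 3). If its buffer received 1%, 5% or 10% of the displaced overdoses, the ratio would be 0.748, 0.741 or 0.732. This stands for the inflation, but not for the inference: 0.75 with nothing prevented is still not an absolute decrease.
- **The planned data can address displacement.** exp(β2) shows the comparator's own change, although mixed with time trend, and the two comparators together carry more information than either alone. This also stands. The detail might be left to an analysis plan, but the protocol itself fixes the wrong reading of each contrast and describes no analysis that would correct it.
- **Pooling is not stated.** A reader might infer from the single treated indicator that both comparators are pooled. Pairing 55 with 55 fits one comparator at a time at least as well.

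**Conclusion.** The concern holds in this form: neither contrast supports the inference attached to it. Treated versus comparator 1 cannot separate an absolute decrease from displacement. The direction of the error is algebraic; its size depends on where displaced overdoses land, from no inflation (0.75) to 0.60 in the example, and the protocol gives neither a displacement share nor a buffer radius. Treated versus comparator 2 keeps any program effect that starts or changes within the 60-day windows, in full: a 10% or 20% fall from other programs would give 0.90 or 0.80 with no remediation effect. Whether such changes occur is an assumption.

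The documents do not show that the Aim 2 estimate is biased. Comparator 1 remains a sound control for other Kensington programs.

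**What to change.** 1. Correct the two rationale sentences in section 3.1, Aim 2, d: comparator 1 controls for other Kensington programs, and neither single contrast is cited as evidence against displacement.
2. Report exp(β3) separately for each comparator.
3. Add a displacement contrast on the geocoded data already planned: treated plus comparator 1, or treated plus a prespecified surrounding area, against comparator 2. Claim an absolute decrease only if that combined count falls. The surrounding area needs its own stated extent, because no buffer radius is given and a ring ending at 0.25 miles would miss displacement beyond it.
4. State the limits. Comparator 2 is adjacent and may receive some displacement. The combined contrast also carries changes in other Kensington programs. Overdoses that land outside the combined area are still missed, so a fall in the combined count is necessary for the claim and does not prove it.

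The cost is a wording change and one more model. The combined contrast is also less precise about overdoses prevented, because the same number is judged against a larger background. If 33 of 132 are truly prevented, the treated-only ratio is 0.75, with |log ratio|/SE = 0.288/0.181 = 1.59. For treated plus comparator 1 the ratio is 231/264 = 0.875. Its SE is √(1/264 + 1/231 + 2/132) = 0.153, so |log ratio|/SE = 0.134/0.153 = 0.88. The protocol should accept that this check may be inconclusive.
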